### Sample size calculation

For both types of fractures (distal radius and ankle), the sample size was determined separately for both patient groups. Based upon a margin of non-inferiority, which is often the smallest value with a clinically important effect [29], of 9 points on the DASH and OMAS (which is based upon what is assumed to be clinically significant [30]) and a standard deviation of 14 [31] and 20 [32], respectively, 70 distal radius and 142 ankle fractures are necessary to demonstrate non-inferiority (power 0.85, alpha 0.05).

To enable a sensitivity analysis for evaluating the study outcomes for two relevant subgroups (that is, conservatively and surgically treated patients), more patients are needed. Based on the empirical treatment ratio for conservative:surgical of 8:2 for distal radius fractures and 5:5 for ankle fractures, we calculated that 142/0.5 = 284 patients with ankle fractures and 70/0.2 = 350 patients with distal radius fractures will need to be included. Accounting for a 10% loss to follow-up means 312 patients with an ankle fracture and 385 patients with a distal radius fracture are to be recruited.

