**Methods/design:**

In a multicenter randomized controlled trial, 697 patients aged 18 years or older will be included: 385 wrist fracture- and 312 ankle fracture patients. Patients will be randomized into two groups: Group 1 receives usual care, consisting of radiographs 1, 2, 6 and 12 weeks post-trauma; Group 2 receives radiographs beyond the initial follow-up only when clinically indicated. The primary outcome is the overall extremity-specific function. For wrist fractures, this includes the Disabilities of the Arm, Shoulder and Hand Score; for the ankle fractures, this includes the Olerud and Molander ankle score. Secondary outcomes include: healthcare cost, the specific function measured with the Patient Rated Wrist and Hand Evaluation for wrist fractures and American Academy of Orthopaedic Surgeons foot and ankle questionnaire for ankle fractures, pain-intensity, health-related quality of life, self-perceived recovery, and complications. Both groups will be monitored at 1, 2, and 6 weeks and 3, 6, and 12 months.

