### Randomization

Randomization of patients will be carried out after obtaining written informed consent using an online randomization program (ProMISe, www.clinicalresearch.nl). Randomization will be stratified by center, type of fracture (distal radius or ankle) and treatment (conservative or surgical). Patients will be randomized into the following two groups.

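### The allowance for 10% loss to follow-up is computed as n × 1.10 rather than n / 0.90, so the recruitment targets of 312 and 385 cover only about 9% loss

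*Protocol article*

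**What the plan says.** The section on sample size calculation builds the recruitment target in three steps.

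1. **Base requirement.** With a non-inferiority margin "of 9 points on the DASH and OMAS", "a standard deviation of 14 [31] and 20 [32], respectively", and "power 0.85, alpha 0.05", the article finds that "70 distal radius and 142 ankle fractures are necessary to demonstrate non-inferiority".
2. **Scaling for subgroups.** So that conservatively and surgically treated patients can be examined separately in a sensitivity analysis, the base numbers are divided by the share of the smaller treatment group: "142/0.5 = 284 patients with ankle fractures and 70/0.2 = 350 patients with distal radius fractures will need to be included".
3. **Loss to follow-up.** The recruitment targets are then given: "Accounting for a 10% loss to follow-up means 312 patients with an ankle fracture and 385 patients with a distal radius fracture".

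The Methods/design part of the abstract carries the result forward as the headline target: "697 patients aged 18 years or older will be included: 385 wrist fracture- and 312 ankle fracture patients".

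**The concern.** The requirement, the loss rate and the target all stand in one paragraph, and they do not agree. If 10% of 312 and 385 recruits are lost, fewer than 284 and 350 remain. The targets look like the requirement plus 10% of itself, which is a common slip: the percentage is applied to the number needed at the end instead of the number recruited at the start.

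The stake is limited. The headline enrolment figure does not deliver the follow-up numbers that the article says it delivers, and the subgroups that determined the size of the trial end slightly below their planned count and planned power.

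**Working it through.** **Inputs.** All come from the sample size section: margin 9 points; SD 14 (DASH) and 20 (OMAS); power 0.85; alpha 0.05; surgical share 0.2 (wrist) and 0.5 (ankle); loss 10%. Two assumptions are needed. The allocation ratio is not stated (the Randomization section says only "Patients will be randomized into the following two groups"), so 1:1 is taken. The sidedness of alpha is not stated either; one-sided 0.05 is taken because it reproduces the base numbers. The true difference is set to zero.

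**Step 1: reproduce the base numbers.** Total N = 4 × SD² × (z₀.₉₅ + z₀.₈₅)² / margin², with z₀.₉₅ + z₀.₈₅ = 1.645 + 1.036 = 2.681.

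- Wrist: 4 × 14² × 2.681² / 9² = 69.6, stated as 70.
- Ankle: 4 × 20² × 2.681² / 9² = 142.0, stated as 142.

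A one-sided 0.025 level would give 88 and 178 (each arm rounded up), which does not match.

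**Step 2: reproduce the subgroup scaling.** 142 / 0.5 = 284 and 70 / 0.2 = 350, both exact.

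**Step 3: identify the loss allowance.** The article prints no formula, so both candidates are tried.

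| | Needed | n × 1.10 | n / 0.90 | Stated |
|---|---|---|---|---|
| Ankle | 284 | 312.4 | 315.6 → 316 | 312 |
| Distal radius | 350 | 385.0 | 388.9 → 389 | 385 |
| Total | 634 | 697.4 | 705 | 697 |

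Multiplication by 1.10 matches both stated targets; division by 0.90 matches neither. The ankle figure was also rounded down from 312.4, so it is a fraction short even under its own rule.

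**Step 4: what the stated targets leave after 10% loss.**

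- Ankle: 312 × 0.90 = 280.8, which is 3.2 (1.1%) below 284.
- Distal radius: 385 × 0.90 = 346.5, which is 3.5 (1.0%) below 350.

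**Step 5: the loss that the targets do cover.** (312 − 284) / 312 = 28/312 = 9.0%, and (385 − 350) / 385 = 35/385 = 9.1%.

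**Step 6: effect on power in the limiting subgroup.** Power = Φ(margin / (SD × √(2/m)) − 1.645), with m patients per arm.

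| Subgroup | Planned size | Power | Size after 10% loss | Power |
|---|---|---|---|---|
| Ankle, either treatment | 142 (m = 71) | 0.850 | 280.8 × 0.5 = 140.4 (m = 70.2) | 0.846 |
| Wrist, surgical | 70 (m = 35) | 0.852 | 346.5 × 0.2 = 69.3 (m = 34.65) | 0.849 |

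**Step 7: effect on the whole-population comparisons.** The same formula with m = 280.8/2 = 140.4 (ankle) and m = 346.5/2 = 173.25 (wrist) gives power of 98.3% and above 99.9%.

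**The case against.** The case on the other side concerns weight, and most of it stands.

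- **Only the subgroup analyses are touched.** The article needs 142 and 70 patients for the main non-inferiority comparisons. After a full 10% loss about 281 and 346 remain, roughly two and five times as many. This is correct, and the point must not be read as a shortfall for the primary question.
- **Loss is not all-or-nothing.** The statistical analysis section plans a longitudinal multilevel model on data at 6, 12, 26 and 52 weeks, with missing data assumed missing at random and not imputed. A patient lost after week 6 still contributes, so 280.8 and 346.5 are complete-follow-up counts and overstate the loss of information. This softens the shortfall; it does not turn 312 and 385 into a 10% allowance.
- **Other inputs are less certain than this.** The treatment split is rounded to 8:2 and 5:5, while the Background gives surgical shares of 18% and 35%. At 18%, 350 wrist patients would include 350 × 0.18 = 63 surgical patients, with power of about 82%. That moves power more than the inflation step does.
- **The formula is inferred.** True, but it matches both targets, and the correct formula matches neither.
- **Restating the loss as 9% fits the assumption to the number.** The article gives no expected loss other than 10%. The 9% should therefore be worded as what the target tolerates, not as a new forecast.

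None of this reconciles the stated figures with one another.

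**Conclusion.** The concern holds as a minor arithmetic error. The targets of 312 and 385, and the total of 697, do not leave 284 and 350 patients after 10% loss; they fall about 1% short, by roughly 3 and 4 patients. A correct 10% allowance gives 316 and 389, which is four more per fracture type and eight in all.

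The counts rest only on figures printed in the article and on reading the loss as a percentage of patients recruited. The power figures also assume a one-sided 5% level, 1:1 allocation, a zero true difference and the article's own treatment split. On those assumptions, power in the limiting subgroups drops by less than half a percentage point and ends just below the planned 85%. No primary conclusion depends on it. It is worth correcting because it sits in the headline target and costs nothing to put right.

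**What to change.** **Preferred.** Keep 312, 385 and 697, and replace the claim of a 10% allowance with a statement that these targets tolerate about 9% loss to follow-up (28/312 = 9.0%, 35/385 = 9.1%) before the numbers fall below 284 and 350. This changes one stated figure and needs no extra patients, which suits a trial that is already enrolling. The final report should describe the sample size in the same way.

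**Alternative.** If the 10% allowance is to stand, change the targets to 316 ankle (316 × 0.90 = 284.4) and 389 distal radius patients (389 × 0.90 = 350.1), and the total to 705, in both the sample size section and the abstract. This costs eight more patients.

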### Statistical analysis

Data will be analyzed using the IBM SPSS version 20 or higher (Armonk, NY: IBM Corp.). Characteristics of the patients in the treatment groups will be presented using descriptive statistics (mean ± standard deviation, median (range) or proportion) to assess if balanced groups were obtained after randomization.

The data analysis will be conducted according to the intention-to-treat principle, with a normal approximation for all questionnaires at 6, 12, 26 and 52 weeks for both types of fractures. For analysis of the primary study outcome, linear and generalized multilevel analyses will be used accounting for dependency within hospitals, clinicians and patients over time (four-level model). This means, among other things, that the data are to be analyzed longitudinally and, thus, the follow-up measurements are to be incorporated in the analyses. Results will be expressed as confidence intervals and these will be subsequently compared to the margin of non-inferiority in order to make inferences about the non-inferiority of the new intervention strategy. In addition to crude analyses, all analyses will also be adjusted for pre-defined prognostic factors, such as age, gender and fracture type. In a secondary analysis, a per-protocol analysis will be conducted which will account for ‘contamination’, meaning those randomized to the intervention group but nonetheless requiring follow-up imaging not allowed in the original treatment design (because there was a clinical indication for imaging).

The secondary clinical outcome measures of quality of life and pain will be analyzed in the same way as the primary outcome measure. The secondary outcome measures of ROM and complications will be compared between the ‘usual care’ group and the ‘reduced images’ group over time.

The cost questionnaires will be used to perform an economic evaluation, which will be conducted from a societal perspective alongside the randomized controlled trial. The aim of the economic evaluation is to measure, value and analyze total costs of patients with distal radius and ankle fractures and to relate the difference in costs to the difference in effects between the intervention group which will receive only the initial follow-up radiographs (at 1 and 2 weeks) and the comparison (that is, usual care) which will receive imaging at the initial follow-up plus at 6 and 12 weeks. Both cost-effectiveness and cost-utility analysis will be performed. The time horizon of the economic evaluation is 12 months. Sensitivity analyses will be performed to assess the robustness of the results using different assumptions regarding costs and effects.

The underlying assumption surrounding missing data for this study is that the data are missing at random. Therefore, given the mixed model approach for the longitudinal analyses, missing data will not be imputed; however, we will correct for baseline covariates thought to be associated with the outcome, such as age, gender, and variables related to the condition (for example, fracture type), as well as variables thought to be related to missingness. In a sensitivity analysis, complete data sets will be compared to incomplete data sets in order to determine how robust these findings are.

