## Methods/design

### Study design

The WARRIOR-trial (Wrist and Ankle fractures Routine RadIOgraphy Reduction) is a multicenter randomized controlled trial using a non-inferiority design.

The trial includes two study populations: distal radius fracture patients and ankle fracture patients. The interventional effects will be analyzed separately for each type of fracture as independent studies. The same design and research questions apply for both studies.

The study will be conducted in three academic hospitals in The Netherlands (Leiden University Medical Center (LUMC), VU University Medical Center Amsterdam (VUmc) and University Medical Center Groningen(UMCG)). This study is approved by the Medical Ethics Committee LUMC for all participating centers (Number P14.086). The trial is registered in the Dutch Trial Register (Nederlands Trial Register NTR4610, registration date 22 June 2014). Study results will be reported following the Consolidation of Standards of Reporting Trials guidelines [12,13].

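### Non-inferiority rests on the intention-to-treat analysis alone, so imaging that departs from allocation could hide a 9-point loss among patients imaged as allocated

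*Protocol article*

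**What the plan says.** The Study design section describes a "multicenter randomized controlled trial using a non-inferiority design", analysed separately for wrist and ankle fractures. The Sample size calculation section sets the margin "of 9 points on the DASH and OMAS".

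The Statistical analysis section states: "The data analysis will be conducted according to the intention-to-treat principle". Confidence intervals are then compared with the margin to judge non-inferiority. Later in the same section: "In a secondary analysis, a per-protocol analysis will be conducted". That analysis is meant to account for contamination, described only for the intervention group and as late imaging that took place because it was clinically indicated. The section does not say that the two analyses must agree, or what is concluded if they differ.

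The section on Group 2 allows late films for new trauma, a pain score above 6, loss of motion, neurovascular symptoms, or at the clinician's discretion with the indication recorded.

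**The concern.** In a superiority trial, departures from allocation usually make success harder. In a non-inferiority trial they make it easier, because they pull the intention-to-treat difference toward zero, where the claim is made.

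Departures can come from three sources: Group 1 patients who miss the routine week 6 or 12 film, Group 2 patients filmed with no listed trigger, and Group 2 leavers, who revert to usual care (Table 1 notes), if their data are still collected. With enough of these, the trial could report that reduced imaging is no worse although patients imaged as allocated lose as much as the margin. The planned per-protocol analysis might show this but could not change the conclusion. The trial is meant to inform a change in national and international protocols, so this matters.

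**Working it through.** **Inputs from the article.** Margin 9; "a standard deviation of 14 [31] and 20 [32], respectively" for DASH and OMAS; "70 distal radius and 142 ankle fractures are necessary to demonstrate non-inferiority (power 0.85, alpha 0.05"; enlarged to 350 wrist and 284 ankle patients for the subgroups. The allocation ratio is not stated ("Patients will be randomized into the following two groups"), so 1:1 is assumed. The sidedness of alpha is not stated either.

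**Reproducing the sample size.** Per arm, n = 2·[SD·(z(1−α) + z(0.85))/9]².
- One-sided 0.05: wrist 34.8, so 35 per arm and 70 in total, as stated. Ankle 71.0 per arm, so 142 in total (144 if 71.005 is rounded up). Power at 142 is 0.850.
- One-sided 0.025: totals 88 and 178, which do not match.

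One-sided 5% is therefore used below.

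**Dilution of the intention-to-treat difference.** Let c be the non-adherent share of Group 1 plus that of Group 2. Assumptions: the true loss is exactly 9 points between patients imaged as allocated; a non-adherent patient has the outcome of the other arm; adherence is unrelated to prognosis; a simple two-arm comparison. Then
- intention-to-treat loss = 9·(1 − c);
- SE = SD·√(4/N): wrist 14·√(4/350) = 1.497, ankle 20·√(4/284) = 2.374;
- P(claim) = Φ(9c/SE − 1.645).

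Example, c = 0.20: wrist Φ(1.8/1.497 − 1.645) = Φ(−0.442) = 0.329; ankle Φ(1.8/2.374 − 1.645) = Φ(−0.887) = 0.188.

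| c | 0 | 5% | 10% | 20% | 30% |
|---|---|---|---|---|---|
| Wrist, N=350 | 0.050 | 0.089 | 0.148 | 0.329 | 0.563 |
| Ankle, N=284 | 0.050 | 0.073 | 0.103 | 0.188 | 0.306 |

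The larger samples sharpen the effect: at c = 20%, the base sizes of 70 and 142 give 0.134 (wrist) and 0.134 (ankle). With a two-sided 95% interval (one-sided 0.025), c = 20% gives 0.224 (wrist, N=350) and 0.115 (ankle, N=284).

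**Requiring both analyses.** The two estimates are treated as bivariate normal with correlation √(n_PP/n_ITT).
- Error with 10 to 30% excluded from the per-protocol set: 0.047 to 0.050. It cannot exceed the 0.05 of an unbiased per-protocol test.
- Power with no true difference and 20% of all patients excluded: wrist above 0.99. Ankle intention-to-treat alone Φ(9/2.374 − 1.645) = 0.984; both 0.957.
- Subgroups of 70 and 142, 20% excluded: power for both 0.756 and 0.754, against 0.852 and 0.850 for intention-to-treat alone.

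At 1:1, c = 20% corresponds to 10% of all patients excluded, so the power loss at 20% excluded is on the cautious side.

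**The joint rule with a selected per-protocol set.** Suppose 20% of Group 2 is excluded and those patients score g points worse than the ones kept (assumption). The Group 2 mean then improves by 0.2·g. For g = 10 the per-protocol loss is 9 − 2 = 7 points. At c = 20%, the joint error is about 0.29 (wrist) and 0.16 (ankle), against 0.33 and 0.19 for intention-to-treat alone. For g = 5 it is 0.15 and 0.10. Only g = 0 returns about 0.05.

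**The case against.** A reader might infer that the trial's false-positive rate is itself well above 5%. The article does not support that. Its aim is to compare a modified follow-up protocol with current care, and for the strategies as randomized intention-to-treat keeps its nominal error. The excess concerns a different quantity, the effect when patients are imaged as allocated. This objection stands and limits the point.

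A reader might also count every late Group 2 film as crossover. The section on Group 2 allows such films on listed triggers and at the clinician's discretion, so those patients are imaged as allocated. Few Group 2 films may be true deviations, and missed Group 1 films are then the main source. This also stands.

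The non-adherence rates are assumptions, and at 5% the rise is modest. The model also assumes that a departure shifts the outcome by the full 9 points.

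The strongest objection is to the remedy. As the article describes it, the per-protocol analysis treats indicated Group 2 films as contamination. If it does so by exclusion, it removes patients selected for pain, stiffness or new trauma and makes the rest of Group 2 look better. Making that analysis co-decisive would look like a safeguard and add little. This stands, and the fix has to include a corrected definition.

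Finally, relying on intention-to-treat alone is a recognised choice, the per-protocol result will be visible, and a fuller plan could hold a rule for disagreement. But the article does fix which analysis leads and which is secondary, so the point is not one it merely left open.

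**Conclusion.** The concern holds in limited form. The plan bases the non-inferiority conclusion on intention-to-treat and gives per-protocol no role in it. The nominal 5% holds for the strategies as randomized. What is unprotected is the conclusion for patients imaged as allocated. If their true loss equals the margin, the chance of a non-inferiority claim is 7 to 9% at an assumed 5% combined non-adherence and 19 to 33% at 20%. These figures rest on one-sided 5%, 1:1 allocation, a full shift of outcome in non-adherent patients, and adherence unrelated to prognosis. How far the risk arises depends on a rate that the article does not give. The change is worth making because it is cheap, but only together with a per-protocol set that agrees with the imaging Group 2 is allowed.

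**What to change.** In the Statistical analysis section:

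1. Reconcile the per-protocol definition with the section on Group 2. Count Group 2 films on a listed trigger, or with a recorded clinician indication, as adherent. Define deviations in both arms: in Group 1, a missed routine week 6 or 12 film; in Group 2, a late film with none of the listed triggers.
2. For the main comparison in each fracture (conservative and surgical together), conclude non-inferiority only if the interval excludes a 9-point loss in both the intention-to-treat and this corrected per-protocol analysis. Otherwise report non-inferiority as not shown.
3. Keep per-protocol results supportive in the conservative and surgical subgroups, where power for both would be only about 0.75.

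The cost is a few sentences and a record of missed and untriggered films. Both analyses are already planned and no extra patients are needed. Power falls slightly in the ankle comparison (0.984 to 0.957 with 20% excluded) and stays above 0.99 for the wrist. Because both analyses must succeed, selection in the per-protocol set cannot create a claim that intention-to-treat does not support. Error control near 0.05 holds only as far as the remaining deviations are unrelated to prognosis.

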#### Group 1 – usual care

Group 1 will receive usual care according to the current national protocol, indicating clinical follow-up as well as radiographic evaluations in the outpatient clinic at 1, 2, 6, and 12 weeks after trauma.

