#### Group 2 – reduced imaging

Group 2 will receive the same clinical evaluations as the usual care group; however, no routine radiographs will be performed beyond the initial 2 weeks. Radiography during follow-up beyond the initial 2 weeks will be allowed if any of the following are present: new trauma to the distal radius or ankle; pain score >6 on the 11-point visual analogue scale (VAS); loss of range of motion (ROM); neurovascular symptoms; at the discretion of the clinician, in which case the indication for radiography is to be recorded in the medical records.

Aftercare apart from radiology will be identical for both study groups and according to the local standards.

At 6 and 12 weeks, 6 months and 1 year, patients will be requested to fill out the questionnaires. The patient can chose between a paper version or a web-based version of the questionnaire. Reminders will be sent when necessary, and attempts will be made to track drop-outs if possible. An overview of follow-up and measurements is provided in Table 1.

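### The 9-point non-inferiority margin is tied to no visit or contrast, and the analysed visits include week 6, which can hardly reflect the omitted radiographs

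*Protocol article*

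**What the plan says.** All references are to the protocol article.

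- Study design: the trial "is a multicenter randomized controlled trial using a non-inferiority design", and each fracture type is analysed as its own study.
- Outcomes: the primary outcome is the DASH (wrist) or the OMAS (ankle). No primary time point is given.
- Sample size calculation: the margin is 9 points on both scales, with "a standard deviation of 14 [31] and 20 [32], respectively". The result is "70 distal radius and 142 ankle fractures are necessary to demonstrate non-inferiority (power 0.85, alpha 0.05". No visit is attached to the margin or to the sample size.
- Statistical analysis: the intention-to-treat analysis runs "with a normal approximation for all questionnaires at 6, 12, 26 and 52 weeks for both types of fractures". The multilevel model means that "the data are to be analyzed longitudinally and, thus, the follow-up measurements are to be incorporated in the analyses". Confidence intervals, in the plural, are then set against the margin. A group-by-time term is neither stated nor excluded.
- Imaging: Group 1 has "radiographic evaluations in the outpatient clinic at 1, 2, 6, and 12 weeks after trauma". In Group 2, "no routine radiographs will be performed beyond the initial 2 weeks" unless there is an indication. Table 1 places randomization at week 2.
- The 12-month horizon in the Statistical analysis section belongs to the economic evaluation only.

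**The concern.** A non-inferiority verdict needs one interval to compare with one margin. This plan yields at least four candidate intervals plus any average of them, and its decision rule does not choose among them.

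One of the four visits is also poorly placed. Scheduled radiographs are the same in both groups at weeks 1 and 2. The first scheduled film that Group 2 misses is due at the week-6 visit, when the first post-randomization questionnaire is also due. A score taken then has had almost no opportunity to be affected by omitting that film. Including it in the deciding quantity, or letting it decide alone, moves the result towards no difference. In a non-inferiority trial that favours the new strategy. With the choice left open, it could also be made after the intervals have been seen.

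**Working it through.** **Inputs from the Sample size calculation section.** Margin 9; SD 14 (DASH) and 20 (OMAS); power 0.85; alpha 0.05; evaluable N of 350 (wrist) and 284 (ankle) after the subgroup inflation.

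**Assumptions.** 1:1 allocation; equal SD at each visit; a common within-patient correlation ρ between visits, shown for 0.3–0.7 because the article gives none; equal visit weights; no allowance for clustering by hospital or clinician.

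**1. The plan's own figure.** n per arm = 2·[SD·(z₀.₉₅ + z₀.₈₅)/9]².
- DASH: 34.79, so 35 per arm and 70 in total, as stated.
- OMAS: 71.005, so 71 per arm and 142 in total, as stated.
- One-sided 0.025 gives 88 and 178, which does not match.

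The stated numbers are therefore those of a single two-group mean comparison at one-sided 5%, and that level is used below.

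**2. If a four-visit average decides.** Take a true loss of 0 at week 6 and 9 at weeks 12, 26 and 52.
- Average loss = (0 + 9 + 9 + 9)/4 = 6.75.
- SE of the average = SD·√(2/n)·√((1 + 3ρ)/4).
- P(non-inferiority declared) = Φ((9 − 6.75)/SE − 1.645).

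| | n per arm | SE, ρ = 0.3 / 0.5 / 0.7 | P(declared) |
|---|---|---|---|
| Wrist | 175 | 1.03 / 1.18 / 1.32 | 70% / 60% / 53% |
| Ankle | 142 | 1.64 / 1.88 / 2.09 | 39% / 33% / 29% |

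A contrast at any single later visit gives 5% in this scenario. With two-sided 95% intervals (1.96 in place of 1.645) the ranges are 40–59% for the wrist and 19–28% for the ankle.

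**3. If any one visit may decide** (simulation of four correlated normal estimates, ρ 0.3–0.7).
- True 9-point loss at all four visits, including week 6: non-inferiority is declared in 12–16% of trials instead of 5%.
- No effect at week 6 and a 9-point loss later: at least 98% for both fractures at the planned N, because week 6 alone nearly always passes.

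**4. If every visit must pass** (true difference zero throughout).
- At 350 and 284: power is above 99.9% (wrist) and 94–96% (ankle).
- At 70 and 142, the size of the smallest subgroup analyses: about 60–70%.

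**5. Power of one named visit at the planned N.** Φ(9/(SD·√(2/n)) − 1.645).
- Wrist: 9/1.497 gives more than 99.9%.
- Ankle: 9/2.374 gives 98.4%.

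**6. Removing week 6 but still averaging.** If the 9-point loss is confined to weeks 26 and 52, an average of weeks 12, 26 and 52 is (0 + 9 + 9)/3 = 6. It passes in 72–86% (wrist) and 41–53% (ankle) of trials.

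**The case against.** Four points can be made for the plan.

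- **Pooling is not in the text.** A reader might infer that the plan averages the four visits and so dilutes a loss as a matter of fact. The article does not say so. Entering all visits in a mixed model is compatible with visit-specific contrasts, and the plural for the intervals leaves that open. Moreover, if the time average were the declared target, a true average of 6.75 would lie inside the margin and passing would be no error. This stands: the figures in step 2 are conditional, and they are errors about the later visits.
- **Zero effect at week 6 is an assumption.** A reader might infer identical imaging up to then. Only the scheduled imaging is identical. Indicated films are allowed in Group 2 after week 2, and questionnaires on paper or web need not precede the visit. This also stands: little effect is plausible, exactly none is assumed.
- **An every-visit rule does not cost the stated power.** A reader might infer that it does. At the planned size of the main comparisons it does not; the loss appears only in groups of 70 and 142.
- **This may sit in an analysis plan.** Model terms often do, and the article is a condensed account. But the article does set out the analysed visits and the decision rule, and that rule does not determine a verdict. Which contrast the margin applies to defines what the trial claims, so this goes beyond missing detail.

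**Conclusion.** The concern holds in this form: the primary non-inferiority decision is tied to no visit or contrast, and the analysed visits include one that can hardly carry the intervention's effect. The size depends on which permitted reading is used.

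- Four-visit average: a 9-point loss at weeks 12–52 would pass in about 53–70% (wrist) or 29–39% (ankle) of trials instead of 5%, under equal weights, ρ 0.3–0.7, one-sided 5% and no effect at week 6.
- Any visit: 12–16% with a 9-point loss at all four visits, and far more if week 6 shows none.
- Every visit: no material problem for the main comparisons.

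The article also does not support reading the sample size as computed for 52 weeks. It reproduces as one two-group comparison, at no named time.

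**What to change.** In the Statistical analysis section, name one deciding contrast per fracture before any analysis. An example is the Group 2 minus Group 1 difference at 52 weeks from the longitudinal model with arm-by-time terms. Because the two scales run in opposite directions, give the sign of the margin: the limit to clear is +9 for the DASH and −9 for the OMAS. State that week 6 does not enter that contrast and is reported descriptively, and that the other visits are supportive.

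The choice of 52 weeks is one defensible option; the requirement is that a single contrast is fixed in advance. An average of the later visits would remove the week-6 problem but could still mask a loss that appears late (step 6).

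The cost is a sentence or two and no new data. A single-visit contrast is somewhat less precise than an average, but the planned N still gives about 98% power or more for it at one-sided 5%.
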